### Study size estimation

In the literature, the likelihood of observing live births without any treatment is estimated to range between 55 and 80% [2]; a multicentre Italian study [9] showed the occurrence of complications in 50% of all untreated women during pregnancy. Given these estimates, for the OTTILIA register, in order to observe an absolute increase of 15–20% (statistical power: 80%, significance level: 0.05), we calculated the inclusion of 190–340 thrombophilic women and, simultaneously, a cohort of pregnant women with the same clinical history (see inclusion criteria) not carrying inherited thrombophilia, in a ratio of at least 1:1. Thus, an overall number of 380–680 consecutive pregnancies are needed.

As far as the FIRST register is concerned, we estimated the inclusion of 624 women. This estimate is calculated on the basis of (1) the probability of observing live births after ART procedures (20–30%), (2) the estimate of an absolute increase of 5–10% in the number of live births after a prophylaxis of LMWHs (statistical power: 80%, significance level: 0.05).

It has been estimated that the OTTILIA and FIRST registries will be executed in the periods February 2012–December 2020 and October 2015–September 2020, respectively. In both the registries, an additional period of 9 months from the date of the last enrollment will be considered.

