### Design and setting of the study

OTTILIA and FIRST registries are two prospective, studies designed to investigate pregnancy or ART outcomes according to different clinical and laboratory features and clinical management in women consecutively observed because of previous reproductive failures after spontaneous or assisted conception, respectively.

The possible assignment of women to treatments (such as LMWH) is not decided in advance but instead falls within current practice.

Obstetrics and Gynecology Departments as well as Thrombosis Centers with local Ethical Committee approval are allowed to participate to these studies.

Authors adhered to SPIRIT guidelines.

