### Statistical analysis plan

Absolute numbers, percentage and median (range) or mean (±standard deviation) will be calculated to describe study groups and sub-groups. Associations between aforementioned primary and secondary outcomes and both numerical and categorical variables (age, drugs, co-morbidities, medical procedures, drug regimens and doses, etc.) collected during study will be tested. Relative risk value, with a 95% confidence interval, will be computed for the comparison of outcomes occurrence.

Validity of primary results will be examined, using a sensitivity analysis of sub-groups and applying more than one statistical test. Parametric and non-parametric statistical tests, according to data distributions, will be used for comparison of categorical and numerical variables. Strategy to prevent missing data will be employed. We select clinical information and laboratory measurements that are routinely included in the ‘real word’ practice, to facilitate the adherence of the investigators to the study protocol. Contacts will be kept with the investigators to reduce the burden of missing data as much as possible. A query-based system will allow us to ask investigators for the missing variables, whether the variables are meaningful for the final analysis. A *p* value below 0.05 will be considered to define statistical significance.

Stratification according to sub-groups of subjects will be taken into account on the basis of propensity to receive or not the treatment. This strategy will allow for an accurate and statistically valid analysis of heterogeneity that will be eventually observed. Potential confounding factors will be identified and after the evaluation of possible relationship between single variables by univariate analysis, logistic regression analysis will be performed to estimate the independence of associations identified. Data analysis will be performed also taking into account type of molecules administered, starting time and duration of thromboprohylaxis.

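### FIRST's 624 women give about 80% power only near a rise in live birth from 20% to 30%; for the 5-point end of the stated range power is roughly 24–32%

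*Protocol article*

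**What the plan says.** Under *Study size estimation*, the protocol article states for FIRST that "we estimated the inclusion of 624 women". It names two inputs. The first is "the probability of observing live births after ART procedures (20–30"%). The second is "an absolute increase of 5–10% in the number of live births after a prophylaxis of LMWHs (statistical power: 80%, significance level: 0.05").

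It does not say which base rate and which increase produced 624. It gives no sidedness and no ratio of treated to untreated women for FIRST. Under *Design and setting of the study*, treatment is left to practice: "The possible assignment of women to treatments (such as LMWH) is not decided in advance". Under *Statistical analysis plan*, a p "value below 0.05 will be considered to define statistical significance", and "Relative risk value, with a 95% confidence interval, will be computed for the comparison of outcomes occurrence".

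The same section handles OTTILIA differently. There a range of effects (15–20 points) is matched by a range of sizes (190–340 thrombophilic women, 380–680 pregnancies in all).

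**The concern.** The required sample size varies roughly with the inverse square of the difference. Halving the increase from 10 to 5 points therefore multiplies the size by about four. A single total tied to 5–10 points, with one power figure for all of it, can be right for part of that range at most.

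Whether LMWH helps is among the primary aims under *Aims*, and the Discussion calls the registries a valid alternative to randomized trials. The Background attributes the inconclusive results of earlier trials partly to small numbers. A reader who takes the stated 80% at face value would think FIRST well placed to show a 5-point gain in live birth, when it would more likely than not miss one.

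**Working it through.** **Inputs.** Total 624, base rate 20–30%, absolute increase 5–10 points, power 80% and significance level 0.05 all come from *Study size estimation*. Two assumptions are added: equal groups (312 v 312) and a two-sided test. The normal quantiles are 1.960 and 0.8416.

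**Formulas** for two independent proportions p1 and p2, with d = p2 − p1 and p̄ their mean:

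- Uncorrected size per group: m = [1.960·√(2p̄(1−p̄)) + 0.8416·√(p1(1−p1) + p2(1−p2))]² / d²
- Continuity-corrected size per group: n = (m/4)·[1 + √(1 + 4/(m·d))]²
- Power at n per group: Φ{[d − 1.960·√(2p̄(1−p̄)/n)] / √[(p1(1−p1) + p2(1−p2))/n]}
- For corrected power, replace n by n − 2/d + 1/(d²n), which inverts the correction.

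**Step 1: reproduce 624.** For 20% v 30%, p̄ = 0.25.

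- First term: 1.960·√0.375 = 1.2002. Second term: 0.8416·√0.37 = 0.5119.
- m = (1.7122)²/0.01 = 293.2, so 294 per group and 588 in total.
- Corrected: (293.15/4)·[1 + √(1 + 4/29.315)]² = 73.29 × 4.2685 = 312.8, so 313 per group and 626 in total.

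The corrected result agrees with 624 to within two women (2 × 312 = 624). The pair is the lowest base rate with the largest increase.

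**Step 2: power at 312 per group, two worked cases.**

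- 20→30%, uncorrected: (0.10 − 1.960 × 0.03467)/0.03444 = 0.931, power 82.4%.
- 20→25%, uncorrected: (0.05 − 1.960 × 0.03343)/0.03337 = −0.465, power 32.1%.
- 20→25%, corrected: effective n = 312 − 40 + 400/312 = 273.3; (0.05 − 1.960 × 0.03572)/0.03566 = −0.561, power 28.7%.

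**Step 3: the corners and midpoints of the stated ranges.**

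| Live birth | Total for 80%, uncorrected | Total for 80%, corrected | Power at 624, uncorrected | Power at 624, corrected |
|---|---|---|---|---|
| 20→30% | 588 | 626 | 82.4% | 79.9% |
| 25→35% | 658 | 698 | 77.9% | 75.3% |
| 30→40% | 712 | 752 | 74.6% | 71.8% |
| 20→25% | 2188 | 2268 | 32.1% | 28.7% |
| 25→30% | 2502 | 2582 | 28.7% | 25.7% |
| 30→35% | 2754 | 2834 | 26.5% | 23.8% |

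The uncorrected totals for 5 points are 2188/624 = 3.5 to 2754/624 = 4.4 times the stated size.

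**Step 4: more generous readings, for a 5-point rise (uncorrected).**

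- One-sided 0.05 test: 38–44%.
- 624 read as the size of each group: 47–56%.
- One-sample test of 25% v 30%: 610 women, close to 624. This would need every woman treated and a fixed historical rate, which does not fit a registry that records who is treated and stratifies on propensity to receive treatment.

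**Step 5: unequal groups (illustrative, uncorrected).** If 25% of women received LMWH, power would be 72% for 20→30% and 22–27% for 5 points. Equal groups are therefore close to the best case.

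**The case against.** The strongest reply is that 624 is a legitimate number. It can be reproduced, the article says only that it was calculated on the basis of those inputs, and a condensed article may omit the pair used. Much of this stands. A reader might infer that 624 was miscalculated; it was not. The article also never says in so many words that FIRST can detect a 5-point gain. However, the objection here is not to a missing detail. The text attaches one power figure to a range, and no two-group reading tried supports that figure at the lower end.

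A reader might also infer that 624 suffices for 20→30% and for nothing else. That is too strong. Without the correction, 22→32% has 80.5% power (77.9% corrected), and 25→35% falls only about two points short of 80%. The shortfall at 10 points is modest; at 5 points it is large.

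A third tempting reading is that a null result will be taken as proof of no benefit. Nothing in the document says so, and the planned confidence intervals would show the imprecision.

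Finally, the article is not consistent on whether live birth is FIRST's primary outcome: the Abstract names clinical pregnancy, and *Study procedure* names live birth or clinical pregnancy. The figures here concern live birth because the sample-size paragraph does.

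**Conclusion.** The point holds in this form: 80% power is wrong as a description of the stated 5–10 point range. It is about right near 20→30%, somewhat optimistic for a 10-point rise from a higher base, and about 50 percentage points too high for a 5-point rise (27–32% uncorrected, 24–29% corrected).

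Equal groups and two-sided testing are assumptions. Relaxing the test to one-sided, or doubling the group size, does not bring the 5-point end near 80%, and the imbalance examined lowers power further. These are unadjusted comparisons; the propensity stratification and logistic regression planned would probably reduce power further, by an amount that the document does not allow to be calculated.

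**What to change.** Replace the FIRST sentence under *Study size estimation* with text along these lines: 624 women, if split equally between LMWH and no LMWH, give about 80% power (two-sided 0.05, continuity-corrected) to detect an increase in live birth from 20% to 30%; by the same method, power for a 5-point increase from a base of 20–30% is about 24–29%, and lower if the groups are unequal. Remove the 80% claim for smaller increases. Use one method for both figures: if the uncorrected formula is preferred, the matching pair is 82% and 27–32%.

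An expected confidence-interval width, or a statement on how a non-significant result will be read, would be an optional addition.

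The cost is wording only. No extra women are needed, and the stated power becomes less favourable.

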### Study procedure

All enrolled women are observed from their first visit after positive pregnancy test (OTTILIA) or before commencing a new ART cycle (FIRST) until the end of pregnancy or ART procedure (negative pregnancy test/end of pregnancy, if successful cycle), respectively.

At baseline, clinical information and index- pregnancy/ART cycle details are obtained from all women by a specially trained staff (Table 2). Data are collected by means of questionnaires and recorded in a web-based database including an electronic form for each woman enrolled. To ensure high quality data, a centralized data management performs quality control and plausibility checks according to predefined procedures. Follow-up data (Table 2) are collected during the three trimesters of pregnancy and in the puerperium period (6 weeks after delivery), at the time of hospital stay, routine clinical follow-up visits or telephone interviews.

**Table 2 Tab2:** Baseline and Follow-up data for evaluation and monitoring of women enrolled in the OTTILIA and FIRST registries

OTTILIA	
Baseline Clinical information: • Maternal age • Body Mass Index • Smoking habit • Reproductive history (previous pregnancies and obstetric complications occurred) • Personal and family history of VTE • Presence of inherited or acquired thrombophilias • Thrombophilic risk factors Index-pregnancy information: • Results of performed imaging tests, (ultrasonography, Doppler ultrasonography) • Invasive prenatal testing (i.e. villous sampling, amniocentesis) • Antithrombotic prophylaxis (brand, doses/day, duration)	Follow-up Pregnancy outcomes: • Live birth (gestational age, delivery mode, sex, birth weight, fetal or maternal hemorrhage) • Obstetric complications (PL, IUFD, gestational hypertension, preeclampsia, HELLP syndrome, SGA newborns, placental abruption) • VTE
FIRST	

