Baseline Clinical information: • Maternal age • Body Mass Index • Smoking habit • Reproductive history (previous spontaneous pregnancies, ART attempts) • Cause of infertility (female, male, mixed or idiophatic), • Personal and family history of VTE • Presence of inherited or acquired thrombophilias • Thrombophilic risk factors Index-ART cycle information: • Fertilization (autologous/heterologous) • Type of ART procedure (IUI, IVF, ICSI, Other) • Ovarian stimulation (brand, doses/day, duration) • Antithrombotic prophylaxis (brand, doses/day, duration), • Number of oocytes retrieved •Number of embryo transfers	Follow-up ART outcomes: • Clinical pregnancy • Live birth (gestational age, delivery mode, sex, birth weight, fetal or maternal hemorrhage) • Obstetric complications (PL, IUFD, gestational hypertension, preeclampsia, HELLP syndrome, SGA newborns, placental abruption) • OHSS (time of occurrence after ovarian stimulation, severity, estradiol levels pg/ml, treatment) • VTE

*VTE* venous thromboembolism, *IUI* intrauterine insemination, *IVF* in vitro fertilization, *ICSI* intracytoplasmic sperm injection, *PL* pregnancy loss, *IUFD* intrauterine fetal death, *SGA* small-for-gestational age, *OHSS ovarian hyperstimulation syndrome*

The primary outcome is the live birth rate in the OTTILIA register and live birth or clinical pregnancy rate in the FIRST. The definition of all primary and secondary outcomes is provided in Table 3.

**Table 3 Tab3:** Definitions of primary and secondary outcomes in the OTTILIA and FIRST registries

	Definitions	Source
Clinical pregnancy	A pregnancy confirmed by ultrasonographic visualization of gestational sac or fetal heartbeat	Wang X et al. Fertil Steril 2003; 79: 577–9.
Live birth	The delivery of a live newborn	https://www.gfmer.ch/Medical_education_En/Live_birth_definition.htm
Pregnancy loss (PL)	A loss occurring ≤20 weeks	Regan L. BMJ 1991; 302: 543–4
Intrauterine fetal death (IUFD)	A loss occurring after 20 weeks	Royal College of Obstetricians & Gynaecologists. Late intrauterine fetal death and stillbrith (Green-top Guideline 55). London: Royal College of Obstetricians & Gynaecologists; 2010 [cited 2019 May 30]
Preterm birth	The delivery of an infant before completion of 37 weeks gestation	ACOG Committee Opinion No 579: definition of term pregnancy. Obstet Gynecol. 2013;122: 1139–40

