Gestational hypertension (GH)	Blood pressure ≥ 140/90 mmHg after 20 weeks of gestation in a previously normotensive woman	www.nice.org.uk/guidance/cg107
Preeclampsia	Blood pressure ≥ 140/90 mmHg and proteinuria of 0.3 g or more in a 24-h urine specimen occurring after 20 weeks of gestation in a previous normotensive woman	www.nice.org.uk/guidance/cg107
HELLP syndrome	Thrombocytopenia (i.e. platelet count < 150,000 cells/μL), elevated AST and/or ALT (> 40 IU/L), increased LDH (> 600 IU/L), and hemolysis (increased LDH level)	Martin JN et al. Am J Obstet Gynecol 1999; 180: 1373–84.
Small-for-gestational age (SGA) newborns	Apparently healthy neonate with birthweight <10th centile for gestational age in the absence of infection and maternal drug or alcohol abuse	RCOG. The investigation and management of the small–for–gestational–age fetus. Green-top Guideline. 2nd ed.; 2014
Placental abruption	The early separation of the placenta from the uterus	Ananth CV, et al. Am J Obstet Gynecol. 2016;214: 272
Ovarian hyperstimulation syndrome (OHSS)	An exaggerated systemic response to ovarian stimulation with a wide spectrum of clinical and laboratory manifestation. According to the degree of manifestations it is classified as mild, moderate, or severe.	Humaidan P, et al. Hum Reprod. 2016;31: 1997–2004
Venous thromboembolism (VTE)	Deep vein thrombosis (DVT), defined as a blood clot in deep veins of the legs with or without pulmonary embolism (PE). DVT is diagnosed if confirmed by Doppler ultrasound exam. PE diagnosis is confirmed by ventilation-perfusion lung scanning, angiography, or computed tomography. Pregnancy-related VTE is defined as a VTE occurring during the pregnancy or in the puerperium (within 6 weeks after delivery).	Kearon C, et al., Chest 2012; 141 (2 Suppl): e419S-e496S.
Hemorrhage.	Bleeding events. They are classified as major or minor according the ISTH criteria. Wound hematoma in case of caesarean section	Schulman S, J Thromb Haemost 2005; 3: 692–4.

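### The nine-month period after the last enrolment is shorter than the observation planned for the last FIRST women, and for the puerperal window in both registries (minor)

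*Protocol article*

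**What the plan says.** The last paragraph of Study size estimation gives the calendar of both registries and then adds: "In both the registries, an additional period of 9 months from the date of the last enrollment will be considered". No derivation is given, and the same period applies to both.

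Study procedure sets the observation of each woman. In OTTILIA it starts after conception: "All enrolled women are observed from their first visit after positive pregnancy test (OTTILIA"). In FIRST it starts earlier and runs "or before commencing a new ART cycle (FIRST) until the end of pregnancy or ART procedure", the pregnancy being followed when the cycle succeeds. The same section then schedules data beyond the end of pregnancy: "Follow-up data (Table 2) are collected during the three trimesters of pregnancy and in the puerperium period (6 weeks after delivery"). Table 3 carries this into an outcome: "Pregnancy-related VTE is defined as a VTE occurring during the pregnancy or in the puerperium (within 6 weeks after delivery").

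The FIRST primary outcome is clinical pregnancy alone in the Abstract, but "live birth or clinical pregnancy rate in the FIRST" in Study procedure. The FIRST sample size is built on live births.

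**The concern.** Two parts of the article do not fit together. Nine months is roughly the length of a pregnancy counted from about conception. FIRST enrolment comes before conception, and the planned data collection in both registries ends six weeks after delivery. Followed literally, the closing period ends before the last women have completed the planned observation.

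If data were closed then, what is missing would depend on the outcome. A negative test or an early loss in a late entrant is known within weeks. A term birth, or a VTE in the puerperium, may not yet have happened. Exposed are FIRST live birth (named as primary in Study procedure and the basis of the sample size) and puerperal VTE (thromboembolic complications are a secondary aim). Study procedure also gives two end points of its own: the end of pregnancy, and six weeks after delivery.

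**Working it through.** **The stated figure.** 9 months = 9 × 365.25/12 ÷ 7 = 39.1 weeks.

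**Inputs from the article.** FIRST entry before the cycle; OTTILIA entry after a positive test; puerperium of 6 weeks; term from 37 completed weeks (Table 3, preterm birth); FIRST 624 women, October 2015–September 2020 (60 months), live-birth rate 20–30%; OTTILIA 380–680 pregnancies, February 2012–December 2020 (107 months), live-birth rate 55–80%.

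**Assumptions, not in the article.** FIRST lead from enrolment to conception of 2–6 weeks; OTTILIA entry at 4–6 weeks of gestation; delivery at 40 weeks unless stated; uniform accrual over the full stated period.

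**Formulas.** Gestation counts from 2 weeks before conception, so:
- FIRST weeks to birth = lead + (gestation at delivery − 2)
- OTTILIA weeks to birth = gestation at delivery − gestation at entry
- End of puerperium = weeks to birth + 6

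| Case | Weeks to birth | Against 39.1 | Weeks to end of puerperium | Against 39.1 |
|---|---|---|---|---|
| FIRST, lead 0, 37-week birth | 35 | inside | 41 | 1.9 over |
| FIRST, lead 2, 37-week birth | 37 | inside | 43 | 3.9 over |
| FIRST, lead 2, 40-week birth | 40 | 0.9 over | 46 | 6.9 over |
| FIRST, lead 4, 40-week birth | 42 | 2.9 over | 48 | 8.9 over |
| FIRST, lead 6, 40-week birth | 44 | 4.9 over | 50 | 10.9 over |
| OTTILIA, entry 4, 40-week birth | 36 | inside | 42 | 2.9 over |
| OTTILIA, entry 6, 40-week birth | 34 | inside | 40 | 0.9 over |
| OTTILIA, entry 8, 40-week birth | 32 | inside | 38 | inside |

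The first row needs no positive lead time: every term delivery in the last FIRST entrant overruns the puerperal window. For a 40-week FIRST birth to be inside, the lead must be no more than 39.1 − 38 = 1.1 weeks.

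**Size in FIRST, if data closed at nine months.** Accrual is 624/60 = 10.4 per month, or about 2.39 per week. Women affected = weekly accrual × weeks over × live-birth rate.
- Births after the close: 2.39 × 0.87 × 0.20 = 0.4 (lead 2) to 2.39 × 4.87 × 0.30 = 3.5 (lead 6). As a share of 624, that is 0.07 to 0.56 percentage points.
- Incomplete puerperia (these include the late births): 2.39 × 6.87 × 0.20 = 3.3 to 2.39 × 10.87 × 0.30 = 7.8.
- With an 8-week lead the upper ends become 4.9 births (0.79 points) and 9.2 puerperia.

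**Size in OTTILIA.** Accrual is 0.82 per week (380 over 107 months) to 1.46 per week (680). Incomplete puerperia: 0.82 × 0.87 × 0.55 = 0.4 to 1.46 × 2.87 × 0.80 = 3.4. With a 40-week birth, no live birth falls outside.

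**The case against.** The strongest reply is that the nine months is a rounded calendar estimate in a sample-size section and not a censoring rule. Study procedure says that all women are observed to the end of pregnancy or procedure and allows telephone follow-up. The Statistical analysis plan section adds contact with investigators and queries for missing variables. This stands in part: nothing says that an open pregnancy is cut off, dropped or counted as a failure. It does not remove the mismatch, because the nine months is the only study-level closing period stated, and a query cannot supply an event that has not yet happened.

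A reader might go further in four ways that the article does not support:

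- **That outcomes will be lost.** This follows only if data are closed at nine months whatever is still open, which the article does not say.
- **That every failure is seen while live births are missed.** Negative tests and early losses would be known, but a late intrauterine fetal death in a last entrant could be missed just as a birth could.
- **That the main outcomes of both registries are at risk.** OTTILIA live birth and FIRST clinical pregnancy are covered.
- **That every late FIRST entrant is an affected outcome.** About 2–12 women enrol too late for a 40-week birth to be seen, and 16–26 too late for a full puerperium. Only the 20–30% who have a live birth contribute, hence the smaller counts in the working.

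Nor is a biased comparison of low-molecular-weight heparin shown. The truncation would be set by enrolment date and would distort the contrast materially only if treatment use differed among the last entrants.

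**Conclusion.** Minor, but wrong as written. The single 39.1-week period cannot hold the observation that Study procedure and Table 3 require of the last women enrolled. For the FIRST puerperium this holds for any term delivery, without assuming a lead time. For FIRST live birth it holds for a 40-week delivery once the lead exceeds about 1.1 weeks; a 37-week birth stays inside with a lead of up to 4 weeks. For the OTTILIA puerperium it holds for a 40-week delivery when entry is before about 6.9 weeks of gestation (46 − 39.1).

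The numerical effect is small: under 1 percentage point on the FIRST live-birth rate, against a planned difference of 5–10 points, and a handful of incomplete puerperia. These sizes depend on the assumed lead, gestation at entry, 40-week delivery and uniform accrual, and on a literal close at nine months. The inconsistency itself does not depend on the sizes.

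**What to change.** In Study size estimation, replace the fixed nine months with a close defined by the women: follow-up continues until every enrolled woman has had a negative test or has reached 6 weeks after the end of pregnancy. Give the expected duration for each registry: about 12 months after the last enrolment in FIRST (46–50 weeks in the working, 52 with a 6-week lead and a 42-week delivery) and about 10 months in OTTILIA (40–42 weeks, 44 with entry at 4 weeks and a 42-week delivery).

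Use the same end of observation in Study procedure, so that the end of pregnancy and the six-week puerperium no longer stand as two different end points.

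The cost is a data lock one to three months later. No further women or visits are needed, because the puerperal data are already planned.
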